### Study Setting

The study will be conducted through the restricted segment of a smartphone app. This app has been especially designed for behavior and opinion research in Brazil and will be used for participant recruitment, assessment of eligibility criteria, delivery and control of the intervention, and data collection.

Currently, the app has registered approximately 1,360,000 active users. Of them, 98,518 have accessed the internet in the past 14 days (September 2020); these individuals will be primarily invited to participate at the recruitment stage, reaching women with different socioeconomic and demographic characteristics in all States of Brazil.

All communication with participants will be carried out within the native and private environment of the app. Engagement will be voluntary, and participants will be financially reimbursed for the value of mobile internet use. The estimated compensation for participation in this study was set between R $5.00 and R $10.00 (US $0.92-$1.84), depending on the extent of participation, to cover the cost of mobile internet usage.

The stages of the study conducted through the app will be comprised of interactive questionnaires (called “missions” in the app), which are opportunities for engagement through direct communication with users. The questionnaires are as follows:

Eligibility criteria filter: the filter has 7 questions related to the study variables (intention to have biological children, number of children, those born through normal delivery, year of birth of the oldest child, race, education, and occupation) (Multimedia Appendix 1)Invitation to participate in the study: information on the study and the investigators, objective of the study, and the dynamics of the missions (Multimedia Appendix 2)Questionnaire to complete and validate the informed consent form: split across different screens, digitally validated by the participant (Multimedia Appendix 3)Entry questionnaire: prospecting of values and preferences associated with the intended care (Multimedia Appendix 4)Questionnaires on childbirth (intervention group) (Multimedia Appendix 5) or on diaper use (control group) (Multimedia Appendix 6)Exit questionnaire: similar to the entry questionnaire (Multimedia Appendix 4)Birth plan questionnaire (Multimedia Appendix 7)

### Participants

All women of reproductive age (18-49 years old) registered on the app will be notified of the invitation to participate in the study in order of priority.

### Eligibility Criteria

To be included in this study, a participant must be a registered user on the app; identify as a woman; be classified under class A, B, C, D, or E in accordance with the Brazil Criteria of 2015 of the Brazilian Association of Research Companies [41]; be aged between 18 and 49 years; and be pregnant or have biological children of any age or intend to have biological children in the future.

### Exclusion Criteria

Women without children and with no intention of having children in the future will be excluded from the study.

### Recruitment

A filter questionnaire will be administered to all women registered on the app and aged between 18 and 49 years, from all Brazilian States and socioeconomic strata. Those who are pregnant or have biological children of any age or intend to have biological children in the future will be notified of the invitation questionnaire to participate in the study. Thereafter, the informed consent questionnaire will be sent to all women who agree to participate in the study. The following stage comprises the entry questionnaire, and all women who digitally provide informed consent will be invited to answer it.

These questionnaires will account for sociodemographic data in addition to those already available on the app’s registry; type of health care assistance and funding (public or private, birth place including the hospital or health care institution, or professional including obstetricians and gynecologists, midwives, and nurse-midwives); clinical-obstetric characteristics (parity, mode of previous delivery, and the presence of a risk diagnosis); perception of safety in childbirth (for the mother and the neonate); and the perception of satisfaction or suffering expected during childbirth (for the mother and the neonate).

### Allocation and Randomization

Users will be recruited through the app, which is voluntarily installed by the user. Registrations are carried out organically, with no active screening for users and no advertising. Once registered, the new user answers questions related to his/her socioeconomic data. Missions will be sent to the profiles of users of all social classes (paired to represent the composition of the Brazilian population in the 5 regions of the country) and aged between 18 and 49 years.

Randomness in the sample is guaranteed in the program architecture of the missions, ensuring that those who undertake 1 mission will not be able to access the other mission, by blocking the mission ID through the execution of filters. On the app screen, the respondent sees only the name of the mission, with no indication of whether that participant is in the intervention or the control arm. To guarantee greater confidentiality and not induce interests or scams, we assigned the same name to the 2 missions: “Being a mother is making choices.” To balance the sample, the statistician team distributes the sample on the basis of the “n” defined for the study, thus generating a balance between the geographical region and economic class.

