**Methods:**

A randomized controlled trial, with 2 arms (intervention and control) and a closed, blind, parallel design, will be conducted with a smartphone app designed for behavior and opinion research in Brazil, with women of reproductive age previously registered on the app. After completing an entry questionnaire to verify the eligibility criteria and obtaining ethical consent, approximately 20,000 participants will be randomly allocated to the intervention and control groups at a 1:1 ratio. Participants allocated to the intervention group will be invited to engage in a digital information and communication strategy, which is designed to expand evidence-based knowledge on the advantages and disadvantages of options for labor and childbirth and the safety of the care processes. The information is based on the guidelines of the Ministry of Health and the World Health Organization for a positive childbirth experience and has been updated to include the new challenges and disruptions in maternity care within the context of the COVID-19 pandemic. The control group will receive information regarding disposable and reusable diapers as a placebo intervention. The groups will be compared in their responses in generating the birth plan and the entry and exit questionnaires, regarding responses less or more aligned with the guidelines for a positive childbirth experience. A qualitative component to map information needs is included.

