## Methods

### Study Design

This study is a randomized controlled trial, with 2 parallel arms (intervention and control) and a closed (only registered app users can participate) and blind design (only the participants are unaware of whether they are in the intervention or control arms). It is registered on the Brazilian Registry of Clinical Trials as “Communication intervention to improve informed choice at childbirth: a randomized controlled trial using digital technology in the context of the Covid-19 pandemic” with the World health Organization unique trial number U1111-1255-8683. The work is being conducted under a program supported by the Brazilian Ministry of Health (Programa de Apoio ao Desenvolvimento Institucional do Sistema Único de Saúde 25000.028646/2018-10).

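### Mission blocking and distribution to a target n are not random assignment, so the allocation text does not support the randomised 1:1 allocation asserted in the abstract

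*Protocol article*

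**What the plan says.** The abstract (Methods) states that "approximately 20,000 participants will be randomly allocated to the intervention and control groups at a 1:1 ratio". Study Design also calls the trial randomised and describes the blinding: "only the participants are unaware of whether they are in the intervention or control arms".

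How the arms are formed is described only under Allocation and Randomization, in three parts:

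- The source of randomness: "Randomness in the sample is guaranteed in the program architecture of the missions". The explanation attached to it is that "those who undertake 1 mission will not be able to access the other mission, by blocking the mission ID through the execution of filters".
- Concealment from participants: "we assigned the same name to the 2 missions".
- Balance: "the statistician team distributes the sample on the basis of the “n” defined for the study". The stated result is that the arms are evened out on region and economic class.

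The section names no random number, sequence, permuted block or minimisation with a random element.

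**The concern.** An article may leave the details of sequence generation to the full protocol, and that alone would be no criticism. Here the article does give a mechanism, and it credits that mechanism with a guarantee it cannot provide. The section also speaks of randomness in the sample and of matching profiles to the national population. Those are matters of representative sampling, not of assignment to arms.

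The trial's causal claim rests on this step. If the stated rule were followed literally, the arm could depend on when or how a woman reached a mission. Study Setting says recently active users are invited first, and Participants says notification follows an order of priority. If missions were also filled in sequence, the arm could track app activity, and engagement is itself an endpoint in Table 1. Data Monitoring and Auditing provides for no monitoring committee and no independent audit, so no outside check would reveal such a pattern.

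**Working it through.** The allocation text contains no figure to reproduce. The check is whether the properties it states imply chance assignment.

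**Step 1. What each stated step delivers.**

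| Stated step | What it secures | What it does not secure |
|---|---|---|
| Blocking the other mission | No woman does both missions | That chance decides which one she does |
| Distribution to the target n | Arm sizes | Chance assignment within those sizes |
| Balance on region and class | Similar arms on two factors | Similar arms on anything else |
| Same name for both missions | Little informed self-selection | Independence of arm from order or time of entry |

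**Step 2. A counterexample.** Suppose that within every region-by-class cell the first half of the women to finish the entry questionnaire got one mission and the second half got the other. Each woman would do one mission only, the arms would reach 10,000 each, and region and class would be balanced. Every property stated in the section would hold, yet assignment would be fixed entirely by order of entry. The stated properties therefore do not imply randomisation. This illustrates the logic; nothing in the documents says it was done.

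**Step 3. What balance on two factors leaves open.** Recruitment lists parity, previous mode of delivery, public or private care, and perceptions of safety and suffering as data to be collected. Study Setting adds preferences recorded in the entry questionnaire. Any of these could differ between arms that match on region and class.

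**Step 4. Who performs the distribution.** Study Design limits blinding to participants. The team that distributes the sample is therefore not described as masked, and nothing in the text rules out discretion.

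**Step 5. Scale.** Inputs are n = 9068 (stated minimum per group) or 10,000 (expected per group), both taken as stated, and two-sided 99% intervals (Statistical Analysis). The prevalence p of the outcome is an assumption, 20% to 50%, because the documents give no prevalence for cesarean preference.

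Half-width = 2.576 × √(2p(1 − p)/n)

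- p = 0.20, n = 10,000: 2.576 × √(0.32/10,000) = 0.0146, or 1.46 points
- p = 0.25, n = 9068: 2.576 × √(0.375/9068) = 0.0166, or 1.66 points
- p = 0.50, n = 9068: 2.576 × √(0.50/9068) = 0.0191, or 1.91 points

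These values assume complete follow-up and an unadjusted comparison. They show how precisely this trial would measure a difference between arms, whatever its source. They do not estimate any bias.

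**The case against.** The strongest defence is that the document does assert randomisation. The abstract says so outright, and the phrase about program architecture may stand for a randomiser that the authors did not describe. The distribution step, tied to region and class, fits stratified randomisation in loose wording. This stands: the text cannot prove that the trial was non-random.

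A reader might infer that a woman's arm is settled by whichever mission she opens first. The documents do not support that. The abstract places allocation after the entry questionnaire and before the invitation to the intervention, and Control or Comparator speaks of women allocated to that group receiving its content. On that order, blocking is a safeguard applied after assignment. The further inference, that women who open neither mission have no arm and that this contradicts the intention-to-treat plan, falls with it. Nor do the documents say that staff place individual women to fill quotas.

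It can also be said that imbalance in prior preference would be visible and adjustable, since preferences are recorded at entry and Statistical Analysis plans an entry-exit comparison and regression on baseline variables. That stands for measured factors. Adjustment does not replace randomisation for unmeasured ones.

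None of this rescues the sentence that derives randomness from blocking.

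**Conclusion.** The point holds as a misstated mechanism. Neither step that the article describes is random assignment, so the description does not support the 1:1 randomisation it claims. Followed literally, it would not secure exchangeable arms. Whether the arms actually were exchangeable cannot be decided from this document.

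No effect size attaches to the point. It is tempting to say that an imbalance of about 2 points in prior cesarean preference would by itself be declared an effect, because 2 points exceeds the half-widths of 1.5 to 1.9. That would require the assumed prevalences, full carry-over of the imbalance to the exit survey and an unadjusted exit comparison. The documents state no such prevalence, plan adjusted analyses and give no sign that an imbalance of that size is likely.

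The section must still be corrected on either reading: in wording alone if a randomiser exists, in conduct as well if it does not.

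**What to change.** Rewrite Allocation and Randomization to state, and use, the following:

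1. A computer-generated 1:1 random sequence, stratified by region and economic class, the factors already named.
2. Assignment by the app, without staff discretion, after the entry questionnaire and before either mission is released.
3. Release of the assigned mission only, with ID blocking kept solely as a safeguard against contamination.
4. An intention-to-treat set made up of every woman assigned.

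Random block sizes and masking of the statisticians are optional additions.

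The Results section puts the start of recruitment in late October 2020, so report the mechanism actually used for women already allocated. If it was random, correcting the text is enough. If it was not, apply the rule above to the remaining women, analyse by allocation period and adjust for baseline preference. The cost of a mid-course change is two allocation regimes in one trial.

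The wording change costs almost nothing and needs no extra participants. If no randomiser exists, the platform's parent company would have to add one; the documents do not say how much work that is.

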### Intervention

The intervention was developed on the basis of the guidelines for childbirth care from the Ministry of Health and the World Health Organization [42-44] updated with reference to the COVID-19 pandemic [45-47]. It is an educational resource to promote women’s knowledge of labor and childbirth care, as well as evidence-based choices for childbirth, which have been shown to protect maternal safety and satisfaction. The intervention consists of dummies, questions, and information cards developed and illustrated especially for this study by author [name], a graphic artist specialized in maternal health.

The intervention presents information regarding the available models of care for childbirth, including information on care provider staff, obstetric practices in labor and childbirth, procedures for perinatal safety, skin-to-skin contact and breastfeeding in the first hour of life, and COVID-19 prevention procedures (Figure 1). The intervention requires the interaction and engagement of participants with the contents presented in a unique electronic “route” format, which will be available for engagement in a restricted segment of the app for 48 hours. After answering all questions, the women will be directed to 1 of the 6 cards with profiles associated with “childbirth styles” (Multimedia Appendix 8).

**Figure 1 figure1:**
[figure not shown]
Screenshot of the app-based intervention: typical childbirth care and COVID-19.

### Control or Comparator

Participants allocated to the control group will receive informative content on models of disposable and cloth diapers that are widely available in the Brazilian market. The theme of disposable diapers versus ecological diapers was selected for the control arm of this trial because it is related to choices in the maternity experience, without interfering with information on labor and birth provided in the intervention arm. The illustrated cards were developed on the basis of the following themes: advantages and disadvantages of each type of diaper; risks of allergies and dermatitis; chemical materials and components; ecological aspects used in manufacturing; decomposition, use of water; and practicality and costs (Multimedia Appendix 6).

### Birth Plan

The birth plan is a structured means of reflecting on the desired care for labor and birth, including an assessment of possibilities and uncertainties arising from the COVID-19 pandemic. It allows assessing the understanding of the intervention through questions on topics such as companionship, mobility, episiotomy, the Kristeller maneuver (fundal pressure), and augmentation with oxytocin. Upon completing the questionnaire (Multimedia Appendix 7), the participant sees her consolidated birth plan and is encouraged to take a screenshot to save this information.

Participants in both the intervention and control arms will be invited to elaborate a birth plan, and we will compare the differences in engagement and the responses.

### Adherence and Study Withdrawal

During recruitment, women of reproductive age will receive app notifications to take part in the study until sample size requirement is fulfilled. Throughout the study, the app will notify participants whenever they have to respond to a questionnaire, and they can save it to respond to it in the next 48 hours. This is intended to guarantee participant engagement in the study, as far it is comprised of 7 questionnaires.

Participants can opt out from the study at any time, withdrawing their consent to participate or simply by the digital act of “aborting a mission.”

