### Data Analysis Plan

#### Statistical Analysis

CONSORT (consolidated standards of reporting trials) guidelines will be used in reporting the results. An intention-to-treat analysis will be performed to compare data from the study's entry and exit surveys. This approach promotes a pragmatic assessment of the potential benefits of the intervention, as it incorporates loss to follow-up in the analyzed data of the intervention group.

Sociodemographic characteristics will be analyzed using descriptive statistics; between-group comparisons will be performed using chi-square analysis or a 2-tailed *t* test. For all group comparisons, the results shall be expressed as an effect (or relative risk for binary outcomes), corresponding 2-sided 99% confidence intervals (α=1%; power=80%), and associated *P* values. Adjusted analyses using baseline variables shall be performed using regression analysis to determine the continuing influence of key baseline characteristics on the outcomes, including female app users in the public and private sectors, cesarean sections, and vaginal delivery. The analyses will be conducted using the R statistical analysis software (The R Foundation) [53].

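### Aborting one mission counts as leaving the study, so stopping the assigned content is merged with withdrawing from outcome collection, and the post-content outcomes are exposed to missing data that may differ by arm

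*Protocol article*

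**What the plan says.** **Leaving the study.** Adherence and Study Withdrawal gives two routes: "Participants can opt out from the study at any time, withdrawing their consent to participate or simply by the digital act of" aborting a mission. The same section lets a woman save a questionnaire and answer it within 48 hours.

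**What a mission is.** Study Setting uses the word for all the interactive questionnaires. Its list places the arm-specific content, "Questionnaires on childbirth (intervention group) (Multimedia Appendix 5) or on diaper use (control group) (Multimedia Appendix 6"), before "Exit questionnaire: similar to the entry questionnaire (Multimedia Appendix 4") and the birth plan questionnaire. The Abstract places allocation after the entry questionnaire, so the content mission is the first step that differs by arm. The Intervention section adds that the childbirth content follows a single route "which will be available for engagement in a restricted segment of the app for 48 hours".

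**Analysis.** Statistical Analysis states: "An intention-to-treat analysis will be performed to compare data from the study's entry and exit surveys". It justifies this "as it incorporates loss to follow-up in the analyzed data of the intervention group". The control group is not named there. Adjusted analyses using baseline variables are also planned.

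**Birth plan.** "Participants in both the intervention and control arms will be invited to elaborate a birth plan". No condition about finishing the content is attached.

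**The concern.** Stopping an assigned intervention and refusing further outcome collection are different events. An intention-to-treat comparison depends on keeping them apart: women who stop the content should still be asked for their outcomes. The withdrawal sentence treats the first event as a form of the second.

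This matters because the content differs by arm. The diaper theme was chosen so as not to interfere with information on labor and birth. The childbirth cards deal directly with those choices, and reduced interest in elective cesarean is a listed endpoint. Women may therefore abort for different reasons in the two arms, and in the intervention arm the reason may be related to the outcome. If so, exit answers would be missing in a way that depends on both arm and outcome, and an analysis plan written later cannot recover answers that the app never requested.

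**Working it through.** **1. The passages side by side.**
- Each questionnaire is a mission (Study Setting).
- Aborting a mission is a way of opting out of the study (Adherence and Study Withdrawal).
- The arm-specific content is a mission that follows allocation and precedes the exit questionnaire and birth plan (Abstract, Study Setting).
- So, read as written, aborting the content is opting out before the outcomes are measured. The article describes no outcome collection after an abort.

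**2. Which outcomes are exposed.**
- Exposed: delivery preference, birth-plan responses and COVID-19 knowledge (Primary Outcomes). Each needs answers given after the content.
- Not exposed in the same way: finishing the missions and developing a birth plan (Table 1). These are proportions in which a woman who stops can be counted as not having the outcome.

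**3. Illustration of size.** The protocol gives no abort or completion rates, so it has no figure of its own to reproduce here.

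Inputs from the protocol: 10,000 women expected per group (Parameters for Calculating the Sample Size) and two-sided α of 1% (Statistical Analysis), critical value 2.576.

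Assumed inputs:
- no true effect;
- elective cesarean preferred by p = 0.15;
- in the intervention arm, abort rates a1 among women with that preference and a0 among the others;
- in the control arm, the same overall abort rate, unrelated to preference;
- an unadjusted comparison of exit answers among completers only.

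Formulas:
- Share completing: c = p(1 − a1) + (1 − p)(1 − a0)
- Preference among intervention completers: q = p(1 − a1)/c. Among control completers it stays at p.
- Completers per arm: n = 10,000 × c
- Expected z = (p − q)/√{[q(1 − q) + p(1 − p)]/n}
- Chance of false rejection ≈ Φ(z − 2.576)

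For 20% v 10%:
- c = 0.15 × 0.80 + 0.85 × 0.90 = 0.120 + 0.765 = 0.885, so n = 8,850
- q = 0.120/0.885 = 0.1356, against 0.15 in control; RR = 0.1356/0.15 = 0.90
- standard error = √[(0.1172 + 0.1275)/8,850] = 0.00526
- z = 0.0144/0.00526 = 2.74; Φ(0.164) = 0.565

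| Abort rate, preferrers v others | Completers per arm | Exit preference, intervention v control | RR | z | False rejection at 1% |
|---|---|---|---|---|---|
| 10% v 10% | 9,000 | 15.0% v 15.0% | 1.00 | 0 | 1% |
| 15% v 10% | 8,925 | 14.3% v 15.0% | 0.95 | 1.35 | about 11% |
| 20% v 10% | 8,850 | 13.6% v 15.0% | 0.90 | 2.74 | about 56% |
| 30% v 15% | 8,275 | 12.7% v 15.0% | 0.85 | 4.31 | about 96% |

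At 20% v 10%, false rejection is about 18% if 5% of women prefer elective cesarean and about 83% if 30% do. Overall loss is equal between arms in every row, so comparing total completion by arm would not reveal the problem.

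**4. What adjustment would do.** In this scenario nobody changes her mind and aborting depends only on entry preference. Each completer then gives the same answer at entry and at exit, so the entry-to-exit change is zero in both arms, and an analysis conditioning on entry preference would show no effect. The table therefore describes the unadjusted comparison only. Adjustment would not remove bias from women who abort because of how they react to the cards, since that reaction occurs after the entry questionnaire.

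**The case against.** The strongest reply is that the withdrawal sentence is a statement of voluntariness. It says how a woman may leave. It does not say that the app then withholds later questionnaires, and the Birth Plan section invites both arms without condition. The detailed schedule is in Multimedia Appendix 9, which was not available here. This stands in part: non-delivery is the natural reading of opting out of the study, but it is not stated. Saving a questionnaire to answer within 48 hours is also not aborting it, so closing the app screen is not the event at issue.

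A reader might go further and infer that the intention-to-treat comparison simply becomes one of women who tolerate the content, and that a spurious fall in elective cesarean preference will follow. The documents do not support that:
- Statistical Analysis says losses are incorporated. How this is done may properly be left to the analysis plan.
- Entry answers and baseline-adjusted analyses are planned.
- Two Table 1 endpoints can count women who stop.
- Nothing shows that women who prefer elective cesarean abort more often. The Abstract describes the content as covering both advantages and disadvantages of the options, the reimbursement rises with the extent of participation, and engagement in the pilot was higher than expected. None of this gives rates by arm.

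The illustration also models differential loss in general. Some women who abort the content would ignore later notifications anyway, so the share of answers that the fix would recover is unknown.

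What the reply does not remove is the merged rule itself. The statement on losses names only the intervention group, whereas aborts can occur in both arms.

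**Conclusion.** The point holds as a design weakness in the written rule. As worded, stopping the assigned content and withdrawing from outcome collection are the same act. This puts delivery preference, birth-plan responses and COVID-19 knowledge at risk of arm-dependent missing data and sits badly with the intention-to-treat comparison.

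The size and direction of any bias cannot be determined from the protocol. The false-rejection figures of about 11% to 96% show what assumed abort rates could do to an unadjusted completers-only analysis; they do not predict this trial's result. The conclusion rests on reading an opt-out as ending follow-up. If the sponsor intends women who abort the content still to receive the exit questionnaire and birth plan, the text needs to say so.

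**What to change.** Amend Adherence and Study Withdrawal so that:
- aborting or not finishing a content mission ends only that mission;
- the exit questionnaire and birth plan go to every allocated woman, on the same schedule in both arms;
- only an explicit choice to leave the study, offered separately when a mission is aborted, counts as withdrawal. The right to leave is unchanged.

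Reconcile the sentence on loss to follow-up in Statistical Analysis with this, so that it covers both groups.

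Cost: a small change to app routing and to the protocol and consent wording, which needs ethics notification because the study is approved and already recruiting, and a few extra notifications to women who stopped the content. The gain depends on how many of those women answer.
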